### Implementation {16c}

The allocation sequence is generated by Prof. [name], Institute of Medical Informatics and Statistics, Kiel University, Kiel, Germany. She will deliver randomization lists (separate for each stratum) to the CTC-A where two staff members not involved in recruitment will be responsible for assigning patients to the intervention. These CTC-A staff members will prepare the respective intervention by filling a weekly medication box with PUFA supplements or placebo.

## Assignment of interventions: blinding

### Who will be blinded {17a}

All involved parties including patients, research staff members responsible for the inclusion and assessment of outcomes, as well as clinical staff delivering standard multimodal AN treatment will be blinded as supplement boxes arrive readily packed and labelled on the ward.

### Procedure for unblinding if needed {17b}

If SAEs or allergic reactions occur, the administration of PUFA or placebo will immediately be stopped until a physician will decide about the further procedure. Sealed envelopes containing the respective assignment are prepared for each patient and will be opened if the principal investigators consider it possible that knowledge of allocation might be beneficial for the patient’s safety.

## Data collection and management

### Plans for assessment and collection of outcomes {18a}

Body weight and height will be measured at each visit. Stool samples will be collected via stool-catching devices and immediately frozen at -80°C. Blood samples will be taken after an overnight fast. Self-reported gastrointestinal complaints are recorded with a shortened 17-item version of the Gastro-Questionnaire [42]. Changes in eating disorder symptoms are assessed by the Eating Disorder Inventory-2 (EDI-2; [43]) and the Eating Disorder Examination-Questionnaire (EDE-Q; [44]) and depressive symptomatology via the Beck Depression Inventory-II (BDI-II; [45]).

Other measures that could also act as confounding variables include obsessive-compulsive symptoms (Yale-Brown Obsessive Compulsive Scale, Y-BOCS; [46]), autistic traits (Social Responsiveness, SRS; [47]) and state anxiety (subscale “state” of the State-Trait Anxiety Inventory, STAI; [48]). In addition, sensitivity for reward and punishment measured by the Behavioral Inhibition System/ Behavioral Activation System scales (BIS/BAS scales; [49]) and impulsivity in form of a tendency to experience negative impulses or feelings in an exceedingly intense manner (subscale “urgency” of the UPPS-P Impulsive Behavior Scale; [50]) will be assessed. As further potential confounding variables comorbid psychiatric disorders will be identified at the first measurement time point using the Mini-International Neuropsychiatric Interview for Children and Adolescents (MINI Kid; [51]) by trained assessors. Six months after inclusion in the study, a short version of the Wechsler Intelligence Scale for children (WISC-V; [52]) and adults respectively for patients aged 17 years or older (WAIS-IV; [53]) will be conducted, i.e. only the two subtests “vocabulary” and “matrix reasoning” will be performed for an estimation of the total IQ.

Moreover, patients and HC will be asked to wear a fitness bracelet (model: Fitbit Flex or Fitbit Flex 2, Fitbit Inc., San Francisco, USA) for 48 h to investigate their physical activity (number of steps and active minutes) and sleep behaviour at all measurement time points.

To gain insight into the food consumption of patients and HC and to be able to perform correlation analyses between calorie content or nutrients and the microbiome composition, the amount of food eaten during 48 h prior to the respective measurement time point will be assessed by food protocols. Patients will additionally be asked to write down their food consumption during the last 48 h before admission to the inpatient treatment.

Furthermore, a series of other variables will be recorded in form of a case report form (CRF) including inter alia demographics and clinical parameters relating to the subtype, onset, and course of disease. For every participant all medication (especially antibiotics) or other supplements taken currently and before the respective measurement time point will be documented in detail.

In order to further examine aberrant cognitive functioning, the Iowa Gambling Task (IGT; [54]) and a Food Go/No-Go task [55] will be analysed. In addition, a probabilistic reversal learning (PRL) task (based on [56, 57]) will be performed to study feedback learning and reward processing in AN.

At TA, those patients participating in the MRI measurements will be asked to fill in a modified version [58] of the Edinburgh Handedness Questionnaire (EHQ; [59]).

The data collection will be conducted by thoroughly trained research staff members in cooperation with the CTC-A. Moreover, detailed standard operating procedures have been established to guarantee a consistent trial conduct over time irrespective of the person performing the data collection.

### Plans to promote participant retention and complete follow-up {18b}

The care system of our department usually accompanies patients with AN for a relatively long period of time after discharge including group psychotherapy offers and often individual psychotherapy, drug monitoring and weighing. Thus, most patients feel attached to our institution and regularly visit the clinic for appointments in the year after the actual discharge. This is advantageous to avoid drop-out in the trial by, e.g., scheduling follow-up meetings together with other appointments. If participants decide to discontinue the intervention, research staff members will endeavour to conduct the follow-up time points anyway including all outcomes to be able to perform intention-to-treat analyses if consent is not withdrawn. If participants refuse to participate in follow-up appointments in person, an effort will be made to inquire the most important outcomes (e.g. height and weight, eating disorder symptomatology, gastrointestinal complaints) via telephone and relevant questionnaires will be sent by mail. If necessary, stool samples can be sent to our department via express shipping as was successfully done in some cases in our pilot study [16].

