### Outcomes {12}

As co-primary outcomes, BMI (kg/m^2^) and overall microbiota community composition, will be analysed at 12-month follow-up. For microbiota community composition, the primary analysis will be based on beta-diversity within and between PUFA and placebo groups, and individual taxa abundance and alpha-diversity will also be considered. While microbiota characteristics do not have a direct translation into clinical relevance, weight restoration is one of the most important aims in the treatment of AN, justifying BMI as a co-primary outcome. Secondary measures include gastrointestinal symptoms, eating disorder psychopathology and comorbid symptoms (measured via questionnaires), physical activity (number of steps measured via fitness bracelets) as well as serum gut permeability and inflammatory markers. Finally, longitudinal changes of the above measures will be compared between patients with AN and HC using data from all four (two for HC) timepoints.

As previous research found clear alterations in cognitive functioning of patients with AN, especially learning abnormalities and aberrant reward processing (e.g. [33–35]), the trial incorporates neuropsychological tests on executive functioning, flexibility and probabilistic feedback learning all presented on a laptop using Inquisit 5 software (Millisecond Software, Seattle, USA, 2016). These neuropsychological measures are considered exploratory outcomes.

Since the study aims at contributing to a deeper understanding of the gut-brain axis in patients with AN, MRI measurements will be performed at three time points (TA, T6 and T12) in a subgroup of 30 patients and at two time points (TA and T6) for 20 HC. The MRI measurements will consist of structural (grey and white matter) scans and diffusion tensor imaging (DTI) and functional MRI scans. The functional MRI scans will include resting state measurements in order to study functional connectivity plus a probabilistic feedback learning task (based on [36, 37]) similar to the neuropsychological test.

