## Statistical methods

### Statistical methods for primary and secondary outcomes {20a}

#### Primary and secondary outcomes

For the co-primary outcome microbiome, the overall community composition will be compared between PUFA and placebo groups using non-parametric analysis based on beta-diversity (Permutational Multivariate Analysis of Variance Using Distance Matrices, [60]), including relevant baseline covariates age, sex, atypical/typical AN, and BMI at admission. For the other co-primary outcome measure BMI (at 12-month follow-up) a mixed-effects model repeated measures analysis will be used to test for superiority of the PUFA treatment vs. placebo. This model will include the covariates age, sex, atypical/typical AN, and BMI at admission. Any available further measurements of BMI (in particular at discharge and month six) will be used. As this is equivalent to a phase II trial, emphasis will be on the 95% confidence intervals of the effect size estimates. Moreover, *p* values will be calculated. For further exploratory analyses of microbiome data, see below.

Secondary outcomes such as eating disorder pathology will be analysed in an analogous way to the primary BMI analysis, additionally adjusting for baseline values of the outcome measure (at admission).

Furthermore, individual taxa abundances will be compared between PUFA and placebo groups using mixed models that account for, e.g. age, sex, medication and baseline or time-specific clinical covariates such as BMI and psychopathology. Correlations between diversity parameters and patient data within time points will be assessed via generalized linear models, whereas mixed models will be applied to assess relationships across time points. Exploratory analyses will associate microbiota community composition data at admission with clinical outcomes and identify characteristics of treatment responders vs. non-responders using “indicator-species” analysis and predictive machine learning algorithms (e.g. random forest models).

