### Methods in analysis to handle protocol non-adherence and any statistical methods to handle missing data {20c}

The primary analysis will be based on the intention-to-treat principle (ITT), including all randomized patients irrespective of the amount of treatment actually received. To follow ITT principle as closely as possible, all participants will be asked to participate in the end-of-treatment and follow-up assessment (at 6 months and 1 year), in particular regarding BMI measurement and providing a stool sample, even if they drop out of treatment, to minimize the amount of missing data. A per-protocol analysis will be performed as sensitivity analysis. To monitor the regular intake of PUFA intervention, the concentration of PUFA in the blood serum will be determined when drawing a blood sample at 6-month follow-up. In this clinical trial, any missing values of the primary outcome variables have to be considered to be missing not at random (MNAR). Patients with very poor response to the intervention and the standard multi-modal treatment of AN that is the same in both arms might be more likely to drop out of treatment and might be more likely not to provide data on the primary outcomes (loss to follow-up). Thus, imputation strategies or analysis methods that rely on the missing at random (MAR) assumption could be anti-conservative. However, every effort will be made to keep missing data as low as possible. In the primary analysis of the primary endpoint, we will use all available measures of the primary outcome BMI at all time points in a mixed-effects model repeated measures analysis.

Sensitivity analyses will be performed to investigate the potential impact of missing data, in particular, by performing a complete case analysis, a pre-specified conservative single imputation approach and by using multiple imputations.

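### BMI obtained by telephone from patients who refuse to attend can enter the co-primary analysis undistinguished from measured BMI, and so bypass the safeguards planned for missing data

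*Protocol article*

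**What the plan says.** BMI at 12 months is one of two co-primary outcomes: "As co-primary outcomes, BMI (kg/m^2^) and overall microbiota community composition, will be analysed at 12-month follow-up" (Outcomes {12}). The standard assessment is direct: "Body weight and height will be measured at each visit" (Plans for assessment and collection of outcomes {18a}).

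The retention section {18b} adds a second route. When a patient refuses to attend, "an effort will be made to inquire the most important outcomes (e.g. height and weight, eating disorder symptomatology, gastrointestinal complaints) via telephone". It does not say who supplies the figure. The same section notes that the department's aftercare includes weighing.

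The section on non-adherence and missing data {20c} states that "we will use all available measures of the primary outcome BMI at all time points in a mixed-effects model repeated measures analysis". The section on primary and secondary outcomes {20a} adds: "Any available further measurements of BMI (in particular at discharge and month six) will be used". Neither separates values by how they were obtained.

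Section {20c} also treats missing primary outcomes as missing not at random. It names "Patients with very poor response to the intervention and the standard multi-modal treatment of AN" as those who may be more likely to drop out and to provide no primary outcome data. It plans three sensitivity analyses for missing data: complete case, a conservative single imputation, and multiple imputation.

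**The concern.** Two rules meet here. One creates an unverified way of obtaining a co-primary outcome, and the other admits BMI values without regard to source. Refusal to attend triggers the telephone route, so it selects patients close to those about whom {20c} is worried. Once a telephone value exists, the patient is no longer missing. She counts as a complete case, and neither form of imputation has anything to replace. The plan's own protection against informative loss then does not reach her.

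If reported weights tend to be too high in this group, a poor responder would appear as an observed, better BMI. If that happens more often in one arm, the estimated difference shifts. The protocol puts its emphasis on the 95% confidence interval of the effect, so even a modest shift touches the main reported result.

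**Working it through.** **Planned figures (Sample size {14}).** Inputs are d = 0.8, two-sided alpha 0.05, 80% power and 1:1 allocation. A two-sample t-test with the noncentral t distribution gives n = 25.52, hence 26 per group, as stated. At 30 per group the power is 86.1% for d = 0.8, 96.8% for d = 1.0 and 69.7% for d = 0.65, against 86%, 97% and 70% stated. The planned figures reproduce, and this point does not alter them.

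**How many patients.** The documents give no telephone share. The planned loss of 10–15% serves as a guide, not a documented bound: 0.10 × 30 = 3 and 0.15 × 30 = 4.5. That is about 3 to 5 per arm if every such patient gave a telephone weight.

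**Formulas.** Let f be the share of telephone values in an arm, b the mean over-report in BMI SD units, and s the SD of any added random reporting error.

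- Bias in the difference = (f_PUFA − f_placebo) × b
- Variance within an arm = 1 + f·s² + f(1 − f)·b²
- Standardised effect = (0.8 + bias) / √(mean of the two variances)

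The ranges for f (0–15%) and b (0.25–1.0) are assumptions. The documents give neither a reporting error nor a BMI SD, so results stay in SD units.

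**Worked case.** Take f = 5% PUFA and 15% placebo, b = 1.0, s = 0.

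- Bias = (0.05 − 0.15) × 1.0 = −0.10 SD
- Variances = 1 + 0.05 × 0.95 = 1.0475 and 1 + 0.15 × 0.85 = 1.1275; mean 1.0875; SD 1.043
- Effect = 0.70 / 1.043 = 0.671; power at 30 per group = 72.5%

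**Range for b = 0.25 to 1.0, s = 0, 30 per group:**

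| Telephone share, PUFA / placebo | Bias (SD) | Power at d = 0.8 | Two-sided type I error |
|---|---|---|---|
| 10% / 10% or 15% / 15% | 0 | 86.0% to 81.8% | 5.0% |
| 5% / 15% | −0.025 to −0.10 | 83.7% to 72.5% | 5.1% to 6.5% |
| 15% / 5% | +0.025 to +0.10 | 88.0% to 90.8% (inflated by the bias) | 5.1% to 6.5% |
| 0% / 15% (extreme) | −0.04 to −0.15 | 82.6% to 67.0% | 5.2% to 8.6% |

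With s = 0.5 and equal shares, power is 85.1% to 80.6%. Equal telephone use therefore costs about 0 to 6 points of power and creates no mean bias.

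**Limits of the calculation.** It uses the t-test of the sample size section, not the mixed model. It also takes telephone use as unrelated to true BMI. If telephone patients were the lighter ones, the spread would grow less, but the bias formula would be unchanged.

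**The case against.** A reader might infer that the protocol enters patients' own telephone reports as if they had been weighed. The text does not go that far. Section {18b} concerns retention and is silent on analysis; pooling follows only from reading it with the unrestricted wording of {20a} and {20c}. Nor does it say that the patient reports the weight. Participants are 12 to 19 years old, and parents are involved in consent and in monitoring capsule intake, so a parent or clinician could supply it.

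Over-reporting is likewise plausible but not documented. The remark in {20c} about poor responders describes those who provide no data, not those who answer the telephone. Double blinding makes the size of any misreporting likely to be similar across arms.

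Numbers should be small. The recruitment section {15} expects no more than 10% drop-out and cites 6% and 4.5% in earlier trials at the institution. On 60 patients that is 3.6 and 2.7. A 15% versus 5% split means 4.5 + 1.5 = 6 of 60, the whole of that 10%.

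Excluding telephone values outright has a price as well: likely poor responders become missing in a mixed model that relies on missing at random, which {20c} itself warns could be anti-conservative.

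Finally, handling by source might be set in an analysis plan that is not shown, and the article does not describe the conservative imputation rule in detail.

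Most of this stands, and it limits the size of the problem and argues against simple exclusion. It does not remove the point. The protocol itself fixes both the telephone route and an inclusion rule without limit by source, and the sensitivity analyses it names address missing data. Blinding does not equalise how many patients refuse to attend. By the protocol's own reasoning, an effective treatment would leave more poor responders, and perhaps more refusals, on placebo.

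**Conclusion.** The point holds in a limited form. Read together, the sections allow unverified BMI values into a co-primary analysis as observed data, beyond the reach of the sensitivity analyses built for informative loss.

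The expected harm is small: a few patients per arm, and no mean bias in the difference unless telephone use or reporting error differs by arm. Under an assumed 10-point imbalance in share and an over-report of 0.25 to 1.0 SD, the bias is 0.025 to 0.10 SD. More over-reported telephone values on placebo would shrink a true benefit; more on PUFA would inflate the estimate. The documents do not support a firm claim of bias in either direction. The change is worth making because it is cheap and because the source of a weight may be hard to recover if it is not recorded at collection.

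**What to change.** 1. Record the source of every weight and height: measured by study staff or a clinician, or reported by telephone, and by whom.
2. Where a measured aftercare weight exists within a pre-specified window around month 12, use it in preference to a telephone value.
3. Add a pre-specified sensitivity analysis of the co-primary BMI outcome that sets telephone values to missing and applies the conservative imputation already planned.
4. Fix before unblinding whether any remaining telephone values stay in the primary model. Either choice is a trade-off between reporting error and further missing data, so it should not be made with results in view.

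The cost is one case-report-form field, one extra analysis, a few sentences of text, and slightly variable timing of some month-12 weights.

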### Data management {19}

Most of the data will be collected directly in digital form on a laptop, so that data entry and the associated errors are avoided. All other data collected using paper-pencil methods will be entered into a web-based database (Open Clinica LLC, MA, USA), while written CRFs will be stored separately enabling later comparison for quality assurance. For these data double entries followed by an automatic computer-based comparison of both versions will be performed and automatic range checks and forced entries (to prohibit missing values) will be conducted. For the neuroimaging data, an automated processing pipeline will be employed to perform timely quality control measurements and consistency checks so that a repetition in case of measurement artefacts will be possible.

### Confidentiality {27}

All data and samples obtained in the trial will be stored securely at the study site in a pseudonymized form allowing no conclusion to be drawn for single participants without the look-up table. Data and samples will be archived for at least 10 years after the end of the study and then anonymized. Imaging data will be anonymized via defacing, i.e. cutting off the front face section that could otherwise be used to reconstruct the participant’s face. The look-up table will be stored electronically, and access limited to staff members that handle inclusion and clinical data acquisition. All documents containing personal information (e.g. the informed consent form) will be stored separately from study records.

Before recruitment of participants started, a data protection impact assessment according to article 35 of the EU General Data Protection Regulation was made that evaluated the risks for rights and freedom of participants and staff in the present trial as low and acceptable.

### Plans for collection, laboratory evaluation and storage of biological specimens for genetic or molecular analysis in this trial/future use {33}

After collection, stool samples will be frozen, divided into three aliquots and stored at − 80°C. To analyse the microbiome composition frozen faecal samples collected from patients and HC will be subject to microbial genomic DNA extraction. Template DNA will be subject to 16S rRNA gene amplicon sequencing or directly (shotgun) sequenced using the Illumina MiSeq or NextSeq platforms, respectively. Blood serum samples will undergo centrifugation and will be separated into aliquots of 500μl and stored at − 80°C. Analysis for inflammatory markers, gut permeability markers and hormones will be conducted using ELISAs.

## Statistical methods

### Statistical methods for primary and secondary outcomes {20a}

#### Primary and secondary outcomes

For the co-primary outcome microbiome, the overall community composition will be compared between PUFA and placebo groups using non-parametric analysis based on beta-diversity (Permutational Multivariate Analysis of Variance Using Distance Matrices, [60]), including relevant baseline covariates age, sex, atypical/typical AN, and BMI at admission. For the other co-primary outcome measure BMI (at 12-month follow-up) a mixed-effects model repeated measures analysis will be used to test for superiority of the PUFA treatment vs. placebo. This model will include the covariates age, sex, atypical/typical AN, and BMI at admission. Any available further measurements of BMI (in particular at discharge and month six) will be used. As this is equivalent to a phase II trial, emphasis will be on the 95% confidence intervals of the effect size estimates. Moreover, *p* values will be calculated. For further exploratory analyses of microbiome data, see below.

Secondary outcomes such as eating disorder pathology will be analysed in an analogous way to the primary BMI analysis, additionally adjusting for baseline values of the outcome measure (at admission).

Furthermore, individual taxa abundances will be compared between PUFA and placebo groups using mixed models that account for, e.g. age, sex, medication and baseline or time-specific clinical covariates such as BMI and psychopathology. Correlations between diversity parameters and patient data within time points will be assessed via generalized linear models, whereas mixed models will be applied to assess relationships across time points. Exploratory analyses will associate microbiota community composition data at admission with clinical outcomes and identify characteristics of treatment responders vs. non-responders using “indicator-species” analysis and predictive machine learning algorithms (e.g. random forest models).

Finally, in addition to the randomized comparison between PUFA and placebo groups, a comparison between HC and patients (in both arms) will be done to assess both differences in gut microbiome composition and diversity between patients with AN and HC in the most acute phase of disease (at admission to inpatient treatment). Furthermore, the size of changes during and after treatment and weight rehabilitation in patients with AN compared to natural fluctuations of microbiome composition in healthy adolescents during normal development will be assessed. Again, mixed-effects models repeated measures analyses with an emphasis on descriptive reporting of confidence intervals of effect sizes will be performed.

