### Objectives {7}

The main objective of this trial is to longitudinally investigate the influence of 6 months PUFA administration on the gut microbiome composition of adolescent patients with AN over the course of hospital treatment and at 1 year follow-up compared to a placebo arm and in comparison to longitudinal changes in gut microbiome composition in healthy adolescents. Primary clinically relevant outcomes will be microbiome composition changes and weight gain. We furthermore want to study the effect of PUFA supplementation on eating disorder psychopathology, comorbidities, and gastrointestinal symptoms. To further deepen our understanding of the underlying pathophysiologic mechanisms, we want to elucidate the influence and interaction of the microbiota with the brain (microbiome-gut-brain axis) by conducting structural and functional Magnetic Resonance Imagining measurements as well as neuropsychological tests in our patients and in a group of HC. In addition, the interaction of the microbiome and inflammation markers, gut permeability, and hormones is investigated to study their role for the potential anti-inflammatory effect of PUFA in AN. Our hypotheses are that PUFA will have an anti-inflammatory effect mediated by the microbiota. Microbiome changes will furthermore lead to a reduction of the “leaky gut” and ameliorate energy utilization of the food consumed. Together, we expect these underlying mechanisms to lead to an increase in weight and a reduction in eating disorder and comorbid psychopathology as well as gastrointestinal symptoms, compared to the placebo group. Comparison to HC will further facilitate the understanding of the basic pathomechanisms of microbiome-gut-brain interaction in AN and help estimate the extent of normalization achieved by our intervention.

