### Trial design {8}

The MiGBAN study is a longitudinal, double-blind, randomized, placebo-controlled superiority clinical trial with an observational HC group. Sixty AN patients will systematically be assessed directly after admission (measurement time point TA; pre-interventional baseline measurement), at discharge (TD), after 6 months (T6; post-intervention) and after 12 months (T12). Randomization to either PUFA or placebo will be performed as a stratified block randomization with a 1:1 allocation ratio. Stratification factors are sex, typical/atypical AN and MRI/non-MRI participation. For the 30 HC, only the measurement time points TA and T6 apply, and these participants will not receive any intervention (see Fig. 1 for an overview of the planned trial design). The trial was approved by the local Research Ethics Committee at the University Hospital RWTH Aachen (reference EK 194/19) and will be carried out in accordance with the Declaration of Helsinki. The study was registered at the German Clinical Trials Register (DRKS00017130, 12 November 2019).

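### The co-primary microbiome test leaves out the patient's own admission microbiome; it remains valid, but may give up precision that is nearly free to recover

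*Protocol article*

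**What the plan says.** The Outcomes section {12} of the protocol article sets the co-primary outcomes and their time point: "BMI (kg/m^2^) and overall microbiota community composition, will be analysed at 12-month follow-up". For the microbiome it adds that "the primary analysis will be based on beta-diversity within and between PUFA and placebo groups".

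The section on primary and secondary outcomes under Statistical methods {20a} names the test: "the overall community composition will be compared between PUFA and placebo groups using non-parametric analysis based on beta-diversity", that is, PERMANOVA, "including relevant baseline covariates age, sex, atypical/typical AN, and BMI at admission". That sentence does not repeat the time point, which comes from the Outcomes section.

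The same section treats the other outcomes as follows. For BMI: "This model will include the covariates age, sex, atypical/typical AN, and BMI at admission". Secondary outcomes are analysed in the same way, "additionally adjusting for baseline values of the outcome measure (at admission".

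Trial design {8} describes admission as "measurement time point TA; pre-interventional baseline measurement". The statistical section also uses admission composition elsewhere: in exploratory prediction of clinical outcomes, and in the comparison of patients with healthy controls at admission.

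**The concern.** The microbiome co-primary is adjusted for the baseline of the other co-primary outcome, BMI, but not for its own. BMI and the secondary outcomes all receive own-baseline adjustment, so the microbiome is the exception.

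If patients differ in composition at admission and part of that difference persists to 12 months, the persistent part stays in the residual of the planned PERMANOVA and dilutes the treatment contrast. This matters more here because the Sample size section {14} has no effect size for microbiome composition. It relies on the expectation that the microbiome effect is at least as large as the BMI effect. The microbiome test therefore has no power margin that anyone has calculated.

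**Working it through.** **1. The plan's own figures.** The Sample size section concerns BMI only. A two-sided two-sample t-test at α = 0.05 with d = 0.8 and 80% power needs 25.5, so 26 per group. With 30 per group, power is 86.1% (d = 0.8), 96.8% (d = 1.0) and 69.7% (d = 0.65). All of these agree with the protocol. With 30 randomised per arm and 10–15% loss, 30 × 0.90 = 27 to 30 × 0.85 = 25.5 remain, so about 26 per arm are evaluable. There is no corresponding figure for the microbiome to reproduce.

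**2. Covariates side by side.**

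| Outcome | Age, sex, AN type | BMI at admission | Own admission value |
|---|---|---|---|
| BMI (co-primary) | yes | yes | yes (same term) |
| Secondary outcomes | yes | yes | yes |
| Microbiome composition (co-primary) | yes | yes | no |

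**3. Scalar analogue.** For one continuous outcome, adjusting for a baseline with correlation r multiplies the residual variance by 1 − r², so a standardised effect d acts like d/√(1 − r²). The protocol gives no r, so it is assumed. With 26 per arm and d = 0.65 (the smallest effect for which the Sample size section gives a power):

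| r | 1 − r² | d/√(1 − r²) | Power | d detectable with 80% power |
|---|---|---|---|---|
| 0 | 1 | 0.65 | 63% | 0.79 |
| 0.3 | 0.91 | 0.68 | 67% | 0.76 |
| 0.5 | 0.75 | 0.75 | 76% | 0.69 |
| 0.7 | 0.51 | 0.91 | 90% | 0.57 |

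This overstates what is attainable here. The full reduction would require adjustment along every axis of composition, and two or three axes remove only part of it.

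**4. PERMANOVA simulations with two or three admission axes.** There were 26 patients per arm. Treatment shifted three axes by the stated number of standard deviations (SD). Effect size, r and the rate at which variance falls off across axes are all assumptions. Sets A and B used 40 axes and 400 trials per cell. In set B, slow and steep decay mean that variance falls by a factor of 0.9 or 0.7 per axis.

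| Set | r | Power as planned | With 2–3 admission axes | Difference (points) |
|---|---|---|---|---|
| A: 0.5 SD | 0.3 | 68% | 65–70% | −3 to +2 |
| A: 0.5 SD | 0.5 | 62% | 69–71% | +7 to +9 |
| A: 0.5 SD | 0.7 | 69% | 86–87% | +17 to +18 |
| B: 0.4 SD, slow decay | 0.7 | 44% | 45–47% | +1 to +3 |
| B: 0.4 SD, steep decay | 0.7 | 52% | 69–71% | +17 to +19 |
| C: 0.4 SD, slow decay | 0.7 | 40% | 47–50% | +7 to +10 |
| C: 0.4 SD, steep decay | 0.7 | 42% | 59–69% | +17 to +27 |

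Monte Carlo error in set A is about 2.5 points. Over all runs with two or three axes, the gain at r = 0.5 was about 0 to 11 points. Rejection under the null was 2.5–5% unadjusted and 3–8% with three axes in set A, and near 5% in set C. Within simulation error these are nominal.

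A separate simulation on Bray–Curtis distances used five axes, so it does not measure this remedy, but it shows the same pattern. Power without and with adjustment was 32% and 29% (stability 0.3), 30% and 38% (0.5), and 25% and 57% (0.7).

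**5. Testing change instead.** An arm-by-time test has relative variance 2(1 − r): 1.4 at r = 0.3, 1.0 at r = 0.5 and 0.6 at r = 0.7, against 1 for the planned test. It is less precise than the planned test whenever r is below 0.5. In simulation at r = 0.3 it cut power from 51% to 38% in one setting and from 40% to 32% in another.

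**The case against.** The strongest reply is that nothing here is an error. The test matches the outcome as defined, and the benefit depends on a correlation nobody has documented. Admission is the acute phase; 12 months comes after refeeding, six months of capsules and possibly antibiotics, so r could be low. The protocol's background says the dysbiosis resolves only in part with weight gain, which leaves room for both persistence and change. This stands, and it is why the gain must be given as a range that includes nothing.

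A second reply is that composition has no single baseline value, and that the choice of distance and axes belongs in an analysis plan not shown here. That holds for the details. The covariate list itself, however, is stated in the article. Four variables are named without the e.g. that marks the later taxa model as open-ended, so the omission reads as a choice.

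Some stronger readings are tempting but unsupported:

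- A reader might infer that the test fails the objective, because Objectives {7} says "Primary clinically relevant outcomes will be microbiome composition changes and weight gain". Under randomisation, expected admission composition is equal in the arms, so a 12-month difference between arms reflects a treatment effect. The same sentence speaks of weight gain where the defined outcome is BMI at 12 months, so it is a loose summary.
- A reader might infer that chance imbalance at admission adds false-positive risk. The permutation test's α already covers it.
- A reader might take admission composition to be the strongest available predictor. That is plausible, but no figure in the protocol shows it.

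**Conclusion.** The point holds as one of efficiency. The planned PERMANOVA is valid and unbiased, and type I error is not at issue. It omits a baseline measurement that the trial will have, against the practice the protocol follows for BMI and the secondary outcomes, in a co-primary test with about 26 evaluable patients per arm.

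The likely benefit of two or three admission axes runs from none (r about 0.3) to as much as 27 points of power (r = 0.7 with variance concentrated in the leading axes). It is small even at r = 0.7 if the variance is spread over many axes. These sizes rest on assumed correlations, effects and variance patterns. The omission itself rests on the text. The change is worth making because the possible gain is sizeable and the cost is small; the trial's conclusions do not depend on it.

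**What to change.** In the co-primary PERMANOVA, add the first two or three principal-coordinate axes of the admission (TA) sample as covariates, entered ahead of the treatment term and alongside the four already listed. Fix the distance measure and the number of axes before unblinding, and state how a patient with a 12-month sample but no admission sample is handled.

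The cost is a change of wording and two or three degrees of freedom. No extra sampling or sequencing is needed, because the planned comparison with healthy controls already requires admission composition to be measured. The protocol does not say that any sample has yet been sequenced, and the remedy does not depend on it. An arm-by-time test should not be substituted: unlike covariate adjustment, it can lose appreciable power when the correlation is low.
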